**Fig. 1 Fig1:**

Schematic illustration of the research design

Twenty-two Victorian secondary schools will be recruited for the study. Schools will be randomly allocated to either receive the intervention immediately or to form a waitlist control group and receive the intervention after completion of the fourth survey. Randomisation will be stratified by the school’s Index of Community Socio-Educational Advantage (ICSEA) score, with two strata defined as <1000 (‘disadvantaged’) and 1000+ (‘advantaged’). The random allocation list will be generated using Stata statistical software, Release 12 (StataCorp, College Station, TX, USA: 2011) with random block sizes of 2 or 4 within each strata.

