**Fig. 3 Fig3:**
[figure not shown]
Consolidated Standards of Reporting Trials (CONSORT) flow diagram of progress through the phases of the MAKINGtheLINK trial

In order to evaluate the main aim of the study, which is to examine the association between participation in the help-seeking programme (control versus intervention arm) and actual help-seeking behaviour at 12 months post intervention, logistic regression analyses will be undertaken testing for group differences between help-seeking behaviour as measured by the AHSQ. In a secondary analysis, gender, depression and anxiety scores, reported alcohol problems, and any characteristics of schools or participants that are imbalanced to a large extent at baseline, will be included in an extended logistic regression model for help-seeking behaviour in addition to the control/intervention arm indicator variable.

For secondary aims, the outcomes are measured by continuous variables, and as such linear regression analysis will be used to compare the two study arms with the primary analysis comprising models with treatment indicator and the baseline value of the outcome score, i.e. analysis of covariance. Secondary analyses will adjust for imbalanced characteristics in the same way as for the primary analysis. All analyses will utilise robust standard errors to adjust for clustering by school.

Each analysis described above will be conducted using participants with all necessary data for that analysis, according to the intention-to-treat principle. Characteristics of participants who were lost to follow-up and who completed follow-up will be compared. Analyses will be repeated using all participants on the basis of multiple imputation involving responses at all four time points to impute for missing values.

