A cluster randomised approach was adopted as this has the advantage of controlling for potential contamination of information between individuals in the same setting (i.e. between control and intervention students in the same school). Our previous experience with MAKINGtheLINK is that the lessons learnt in the classroom are often embraced by the school community, and as such, individual randomisation within a school setting would have created additional confounds. Including measures of school disadvantage, as well as other demographic and clinical data, provides an opportunity to explore predictors of help-seeking outcomes within particular school environments, as well as how the intervention is influenced by current mental health symptoms and past help-seeking behaviour.

A number of changes were made to the programme that built on the findings from the two pilot studies. These studies demonstrated that the programme was both highly feasible and acceptable within school settings [15], and led to an initial reduction in help-seeking barriers and increase in intentions to seek help from formal sources [16]. However, these effects were not consistently maintained at follow-up 6 weeks later, as participants’ help-seeking intentions had returned to baseline levels at this time point. In response to these findings, the programme was expanded to include the addition of a booster session 1 month after the initial intervention, given evidence that this can increase retention of knowledge and improve outcomes. The booster session provided students with a second opportunity to practice help-seeking skills using a different video scenario of a young person struggling with personal issues, as well as a poster-making activity that provided students with the opportunity to share their knowledge with other year groups. Materials from the two previous pilots were further refined, with additional mental health examples and case studies added to the programme, as well as a discussion of the mental health continuum, which increased the length of the overall intervention. Teacher training was offered to staff across the school, and a newsletter was provided to staff to ensure that they were aware of the agreed referral process within the school and were able to provide a helpful response if approached by students.

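### Schools are randomised within two ICSEA strata, but no model comparing the arms includes the stratum by specification, so standard errors are too large if ICSEA is prognostic

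*Protocol article*

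**What the plan says.** Under Study design, the protocol article states: "Randomisation will be stratified by the school’s Index of Community Socio-Educational Advantage (ICSEA) score". There are two strata, below 1000 and 1000 or above, with random blocks of 2 or 4 schools within each. Twenty-two schools are to be recruited.

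The Statistical analysis section then describes the models:

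- **Primary outcome:** "logistic regression analyses will be undertaken testing for group differences between help-seeking behaviour as measured by the AHSQ". No covariate is named.
- **Extended logistic model:** gender, depression and anxiety scores, and alcohol problems. In addition, "any characteristics of schools or participants that are imbalanced to a large extent at baseline, will be included in an extended logistic regression model". These terms are "in addition to the control/intervention arm indicator variable".
- **Continuous secondary outcomes:** analysis of covariance, described as a "primary analysis comprising models with treatment indicator and the baseline value of the outcome score". Secondary versions adjust for imbalanced characteristics as above.
- **Variance:** "All analyses will utilise robust standard errors to adjust for clustering by school".

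The ICSEA stratum is a named term in none of these.

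**The concern.** Blocking within strata keeps the arms nearly balanced on ICSEA, so a difference in outcome between strata largely cancels from the comparison of arms. The true sampling variance of the treatment effect falls accordingly. A model without the stratum still counts that difference as unexplained variation between schools. Clustering the standard errors by school does not remove it, because it sits in the school-level residuals. The reported standard error then exceeds the true one: intervals are too wide and the test rejects too rarely under the null.

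The only route by which ICSEA could enter works against the design. Entry depends on a large observed imbalance, which stratified allocation is meant to prevent, and so a factor fixed before randomisation is left to a data-dependent rule. At stake is precision, in the primary comparison above all.

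**Working it through.** **Inputs from the article (Sample size calculation and Study design).** Difference in proportions 0.064; pooled SD 0.188; ICC 0.05; 51 students analysed per school; two-sided alpha 0.05; power 80%; 22 schools, taken as 11 per arm.

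**Input not in the article.** R², the share of between-school variance explained by the ICSEA stratum. It is assumed and varied from 0 to 0.50.

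**Reproducing the planned size.**

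- Individuals per arm: 2 × [0.188 × (1.960 + 0.842) / 0.064]² ≈ 135.5, rounded up to 136.
- Design effect: 1 + (51 − 1) × 0.05 = 3.5.
- 136 × 3.5 = 476 per arm, as stated.
- 476 / 51 = 9.33, so 10 schools per arm; 20 × 51 = 1020; 1020 / 0.75 = 1360.

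All stated figures reproduce, and none takes credit for stratification. By the same formula, power is 82.8% with 10 schools per arm and 86.2% with 11.

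**Effect of omitting the stratum (normal approximation, arms balanced within strata, k = 11 schools per arm).**

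- Variance that the model without the stratum reports: V_rep = 2 × 0.188² × (0.05 + 0.95/51) / k. The bracket is 0.0686 and the SE is 0.0210.
- True variance under stratified allocation: V_true = 2 × 0.188² × (0.05 × (1 − R²) + 0.95/51) / k.
- SE ratio = √(V_rep / V_true).
- Actual alpha without the stratum = 2 × [1 − Φ(1.96 × SE ratio)].
- Power without the stratum = Φ[(0.064 − 1.96 √V_rep) / √V_true].
- Power with the stratum = Φ[0.064 / √V_true − 1.96].

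| R² (assumed) | bracket in V_true | SE ratio | alpha without stratum | power without | power with | points forgone |
|---|---|---|---|---|---|---|
| 0 | 0.0686 | 1.00 | 0.050 | 86.2% | 86.2% | 0 |
| 0.10 | 0.0636 | 1.04 | 0.042 | 87.1% | 88.6% | 1.5 |
| 0.25 | 0.0561 | 1.11 | 0.030 | 88.5% | 92.1% | 3.6 |
| 0.50 | 0.0436 | 1.25 | 0.014 | 91.4% | 96.9% | 5.5 |

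The SE ratio depends only on the ICC, the cluster size and R². The power columns also depend on the planned difference and SD.

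**Simulation check.** School-level simulation on the same scale, strata of 10 and 12 schools, 20,000 runs per setting, ordinary cluster-robust SE with a t reference on 21 df:

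| R² | alpha without / with stratum | power without / with stratum |
|---|---|---|
| 0 | 0.057 / 0.064 | 84.0% / 85.2% |
| 0.10 | 0.048 / 0.063 | 84.6% / 87.5% |
| 0.25 | 0.035 / 0.061 | 85.7% / 91.2% |
| 0.50 | 0.016 / 0.062 | 88.8% / 96.6% |

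The direction and the conservative alpha agree with the approximation. The adjusted analysis runs at about 0.06 because an uncorrected robust variance is too small with 22 clusters. Part of the simulated power gap is therefore not real gain: at R² = 0 the adjusted model already appears 1.2 points better.

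**The case against.** The strongest reply is that this is a condensed article, and that carrying the stratifier into the models is a detail for the statistical analysis plan. That would carry weight if the article were silent on covariates. It is not: it fixes the covariates of the covariance models, lists those of the extended model, and sets the rule by which anything else enters. Followed as written, that leaves the stratum out. The reply is fairer for the primary logistic model, where an arm-only model is inferred from the contrast with the extended one.

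It is also true that ICSEA is not barred from every model. The extended models admit largely imbalanced school characteristics, and with 22 schools and incomplete blocks some residual imbalance is possible. The Discussion adds: "Including measures of school disadvantage, as well as other demographic and clinical data, provides an opportunity to explore predictors of help-seeking outcomes". That is exploratory and names no treatment-comparison model.

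The error is conservative. It neither biases the comparison nor inflates false positives. For the covariance models, the baseline score may already absorb some of any ICSEA association.

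A reader might infer that the power gained by the design is thrown away, or that the trial is underpowered as a result. The documents support neither. The 476 per arm never relied on stratification, and the analysis without the stratum keeps part of the gain (86.2% rising to 87.1%, 88.5% and 91.4%).

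A logit-scale simulation can give a far larger loss, for example 37% power without the stratum against 58% with it. That case assumes 21% versus 30% seeking help, proportions the article does not contain. It also adds a 1.0-logit stratum difference to a school SD of 0.42. That SD alone gives a latent ICC of 0.176 / (0.176 + 3.290) = 0.051, the article's whole ICC. Equal strata 1.0 logit apart add 0.25, raising it to 0.426 / (0.426 + 3.290) = 0.115, with ICSEA explaining 0.25 / 0.426 = 59% of between-school variance. With total school SD held at 0.42 and the same assumed proportions, power without the stratum stayed at 51–52% for stratum shares from 0 to 50%, against 54%, 58% and 67% with it at shares of 10%, 25% and 50%. There is something to gain, but no collapse.

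**Conclusion.** The point holds in a limited form. The stratification factor is in no treatment-comparison model by specification, and clustering by school does not make up for it. If ICSEA explains 10% to 50% of between-school variance, the standard error is about 4% to 25% too large, and on the planning inputs about 1.5 to 5.5 points of power are forgone. The SE figure is the one to rely on, since points forgone vary with where the trial sits on its power curve. The article gives no association between ICSEA and help-seeking, so the size cannot be narrowed; it is zero if there is none. No figure stated in the article fails, and validity is not threatened. The change is worth making because the precision is lost needlessly and the remedy is nearly free.

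**What to change.** State, before the data are analysed, that the two-level ICSEA stratum is a fixed covariate in the primary logistic model, the covariance models and the extended models, whatever the observed balance. In the same place, name a small-sample correction to the robust standard errors suited to 22 schools, so that alpha does not exceed 5% once the stratum is in.

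The cost is one or two sentences and one school-level degree of freedom. No new data are needed, since the stratum of every randomised school is known. The odds ratio becomes conditional on stratum, and the plan should say so.

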### Sample size calculation

Sample size calculations accounting for cluster randomisation have been estimated using Stata 12 software (StataCorp, College Station, TX, USA: 2011). Useful background information is available from a controlled pre-post pilot study conducted in three regional high schools that were matched on socioeconomic characteristics [18]. The trial group included 171 year-11 students from mainstream classes who received a school-based intervention (Building Bridges to General Practice) that addressed adolescents’ psychological help-seeking barriers in presentations delivered by trained general practitioners (GPs) [18]. At baseline, only 1 (0.6 %) of the 171 students reported visiting a GP. At 12-week follow-up, 12 students (7.0 %) indicated receiving a consultation. Assuming the pre-test consultation rate represents the control group post measure for the proposed trial, we estimated the effect size in schools (where the intervention is implemented by trained staff as the expected difference in proportions between the control arm and the intervention arm) to be 6.4 % (pooled SD 18.8 %). Assuming 80 % successful consent and randomisation, followed by a 25 % attrition rate between baseline and follow-up, the number of students in the analysis would be 60 % of a school’s year-9 level. We anticipate that this will lead to an approximate average cluster size for analysis of 51 students per school.

It is important to note that the assumed effect size may be a conservative estimate considering the intervention’s focus on help-seeking from both formal and informal sources, rather than just GPs, who young people are reluctant to access. In other words, both the prevalence at baseline and the difference in proportions at 12-month follow-up, of students seeking help from formal and informal sources are likely to be greater than the pilot study indicates for seeking help from GPs.

For the proposed project, the intra-class correlation (ICC) is unknown, although a comparable school-based cluster randomised trial conducted by Jorm and colleagues reported an ICC of 0.05 [19]. Setting ICC (ρ) at 0.05, power (1 − β) at 80 %, and a two-sided level of significance at 5 % (*α* = 0.05), the required number of individuals per treatment arm is 476 students corresponding to a need for 10 schools per arm. The desired sample size was 1020 and this was increased to 1360 to allow for 25 % dropout by the 12-month follow-up assessment.

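### Robust standard errors with 20 to 22 schools and no stated small-sample correction leave the size of the primary test uncontrolled, at about 7–10% instead of 5% if the ICSEA strata explain little

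*Protocol article*

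**What the plan says.** The Statistical analysis section plans a logistic regression of actual help-seeking on trial arm as the primary analysis, and linear models adjusted for baseline for the continuous secondary outcomes. One sentence covers clustering for all of them: "All analyses will utilise robust standard errors to adjust for clustering by school". It names no variance variant, degrees of freedom or reference distribution, and the primary model as described has no term for the randomisation stratum.

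The number of schools is fixed elsewhere. Study design states "Twenty-two Victorian secondary schools will be recruited for the study" and stratifies their allocation by ICSEA score into two strata. Sample size calculation arrives at a figure "corresponding to a need for 10 schools per arm", tested at "a two-sided level of significance at 5" per cent, with an "approximate average cluster size for analysis of 51 students per school". It also says that "the intra-class correlation (ICC) is unknown" and borrows 0.05 from a comparable school trial. The Sample section admits schools with 40 to 250 year-9 students.

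**The concern.** Treatment varies only between schools, so the arm comparison rests on 10 or 11 independent units per side. The cluster sandwich variance is justified when clusters are many. With few clusters it is too small on average and is itself imprecise, and a normal reference allows for neither fault. Unequal school sizes make both worse. The primary p-value would then overstate the evidence and the primary interval would be too narrow. The Discussion ties a successful result to adoption in a national school framework, so the false-positive rate of this test matters.

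**Working it through.** **The plan's own figures.** The inputs from Sample size calculation are a difference "to be 6.4 % (pooled SD 18.8" per cent, 80% power, two-sided 5%, ICC 0.05 and 51 analysed per school.

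- Unclustered: n = 2 × (1.960 + 0.842)² × (0.188/0.064)² = 135.5, so 136 per arm.
- Design effect: 1 + (51 − 1) × 0.05 = 3.5, and 136 × 3.5 = 476 per arm, as stated.
- Schools: 476/51 = 9.3, so 10 per arm. Then 2 × 10 × 51 = 1020, and 1020/0.75 = 1360, as stated.

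The sample size reproduces. It uses a normal reference throughout.

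**Type I error with equal school sizes, closed form.** Let G be the number of schools and g = G/2. The plain sandwich variance is (g − 1)/g times the pooled between-school variance. The commonly used factor G/(G − 1) restores part of that. If v is the resulting ratio, a test against 1.96 has true size P(|t(G−2)| > 1.96 × √v).

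| | v | 1.96 × √v | Size |
|---|---|---|---|
| 20 schools, plain | 9/10 = 0.900 | 1.859 | 7.9% |
| 20 schools, with G/(G−1) | 0.900 × 20/19 = 0.947 | 1.908 | 7.3% |
| 22 schools, plain | 10/11 = 0.909 | 1.869 | 7.6% |
| 22 schools, with G/(G−1) | 0.909 × 22/21 = 0.952 | 1.913 | 7.0% |

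This needs no assumption about variation in school size or about prevalence.

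**Type I error by simulation.** There were 40,000 null trials per setting (Monte Carlo standard error about 0.15 points), with beta-binomial outcomes, a logistic model with arm only, ICC 0.05 and no stratum effect. The plan's 60% analysed share turns the eligible 40–250 students into about 24–150 per school. The coefficients of variation (CV) of school size and the prevalences are assumptions. Ranges cover 20 and 22 schools and prevalence 7–35%.

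| School sizes | Plain, normal | G/(G−1), normal | G/(G−1), t(G−1) | Kauermann-Carroll, t(G−2) | Mancl-DeRouen, t(G−2) |
|---|---|---|---|---|---|
| Equal | 7.2–8.8% | 6.6–8.1% | 5.3–6.4% | 4.7–5.7% | 3.7–4.7% |
| CV 0.5 | 8.8–10.3% | 8.2–9.5% | 6.6–7.7% | 5.5–6.5% | 4.3–5.1% |
| CV 0.65 | 9.6–11.3% | 8.9–10.5% | 7.2–8.4% | 6.0–7.0% | 4.4–5.2% |

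The borrowed ICC hardly matters. At CV 0.5 and prevalence 20%, an ICC from 0.01 to 0.10 gives 7.9–9.9% with a normal reference. At the 0.6% prevalence assumed for controls in the sample size, 34–44% of null trials have an arm with no events and the test breaks down, so that setting is left out of the ranges.

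**Effect of stratified randomisation without a stratum term** (CV 0.5, prevalence 20%, balanced strata, normal reference, with and without the G/(G − 1) factor, 20 and 22 schools):

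| Share of between-school variance explained by ICSEA | Size |
|---|---|
| 0% | 8.1–9.5% |
| 10% | 7.2–8.2% |
| 20% | 6.3–7.0% |
| 30% | 5.1–5.7% |
| 50% | 3.3–4.0% |

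**Power at the plan's effect.** With 22 schools the standard error is 0.188 × √(2 × 3.5/561) = 0.0210, so the non-centrality is 0.064/0.0210 = 3.05. Power is 86.2% with a normal reference, and 82.6% with t(20), critical value 2.086. With 20 schools the non-centrality is 2.91. Power is 82.8% with a normal reference and 78.5% with t(18).

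**The case against.** The strongest reply is that the article never says the standard errors will be uncorrected. A Mancl-DeRouen variance is also a robust standard error, and a condensed article may leave the variant and degrees of freedom to an analysis plan that is not shown. Stata 12 is named only for the sample size and the allocation list, so its defaults cannot settle the matter. This stands as a limit: the inflation is conditional on the ordinary reading of the sentence. It does not remove the point. The article does choose a method, applies it to every analysis, and pairs it with a number of schools for which the ordinary version is unreliable.

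A reader might infer that the plan carries a fixed false-positive rate of 8–9%. The documents do not support that. The figure depends on assumed size variation and prevalence, since 40 to 250 is an eligibility range and not a distribution. It also leaves out the ICSEA stratification, which lowers the error and could bring it to 5% or less.

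A reader might also extend the inflation to every secondary outcome, or expect it to grow when school-level covariates are added. Neither was computed. The secondary outcomes use linear models, where a t reference may apply and the inflation would be smaller. The extended model is a secondary analysis whose named covariates are measured on individuals; school characteristics enter only if they are largely imbalanced at baseline.

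**Conclusion.** The point holds in conditional form. With the ordinary cluster sandwich and a normal reference, and with strata that explain little, the primary logistic test runs at about 7–8% with equal school sizes and about 8–10% with moderately unequal ones, reaching 11.3% at the most unequal sizes and lowest prevalence in the range. If the strata explain some 30% of the between-school variance, the omitted stratum term happens to cancel the bias; beyond that the test becomes conservative. The plan gives no value for that share. The defect is therefore that the size of the primary test is left to two unquantified errors in opposite directions. It is not that any single inflated rate is established.

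**What to change.** Replace the clustering sentence with a statement to this effect: the primary and secondary analyses use a small-sample bias-corrected cluster-robust variance (Mancl-DeRouen), include the ICSEA stratum as a model term, and base tests and confidence intervals on a t distribution with degrees of freedom equal to the number of schools minus the number of school-level parameters. A permutation test of allocation within ICSEA strata can serve as a check. Mancl-DeRouen is preferred because Kauermann-Carroll with t(G−2) still gives about 5.5–6.5% at CV 0.5.

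The cost is analysis wording and slightly wider intervals. With t(G−2), 22 schools keep 82.6% power at the plan's effect, while 20 schools fall to 78.5%, just under the 80% target. Counting intercept, arm and stratum leaves 22 − 3 = 19 degrees of freedom (critical value 2.093); the same non-centrality of 3.05 then gives 82.4%, before any gain from the stratum term. The simulations of the corrected variances used arm only, so the version with the stratum term should be checked when the wording is settled.
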